### Criteria for discontinuing or modifying allocated interventions {11b}

In patients with impaired renal function (creatinine > 120 μmol/L), the dose will be reduced to 1000 mg tranexamic acid.

### Strategies to improve adherence to interventions {11c}

As this is a single intervention study, the medication will be administered once during surgery, and no measures will be taken to improve adherence.

### Relevant concomitant care permitted or prohibited during the trial {11d}

Correction of coagulation and transfusion will be at the discretion of the attending anesthesiologist. The laboratory results taken for this study will not be available for the attending anesthesiologist. Furthermore, the perioperative surgical hemostatic measures (i.e., adrenaline-soaked gauzes and subcutaneous adrenaline injection) will be at de discretion of the performing surgeon appropriate to the local protocol. As such, the concomitant care remains similar between groups.

### Rescue medication

In the event of massive, uncontrollable bleeding, leading to multiple transfusion and the need for correction of the coagulation, patients will be given 1000 mg of tranexamic acid, regardless of the original randomization.

### Provisions for post-trial care {30}

After completing the trial, participants will be treated with the standard of care.

### Outcomes {12}

Primary outcome:The volume of blood loss in milliliter/% BSA excised measured during surgery

Secondary outcome:The occurrence and magnitude of fibrinolysis/coagulopathy during burn excisional measured by, among others, ROTEM-analysis, the measurement of global fibrinolysis and D-dimerGraft take of the split skin graft on the area of excision measured in the percentage of vital graft 5 days surgeryHospital mortalityLength of (ICU) stayCardiopulmonary (i.e., arterial embolism)/ neurologic complication (i.e., stroke) (at 3 months after the study procedure)Need for escape medication (tranexamic acid 1000 mg) in case of uncontrolled bleedingThe need for red blood cell transfusion peri-procedural

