**Fig. 1 Fig1:**
[figure not shown]
SPIRIT figure, schedule of enrolment, interventions, and assessments. -t_1_: > 24 h before surgery; t_1_: pre-surgery; t_2_: after anesthesia induction but before incision; t_3_: 1 h after incision; t_4_: during closure if total surgery time > 1.5 h; t_5_: end of surgery; t_6_: > 6 h after finishing surgery. *Blood samples*: hemoglobin, electrolytes (sodium/potassium), kidney function (urea/creatinine), albumin. *Basic coagulation*: INR, APTT, thrombocytes and fibrinogen. *Additional coagulation*: plasminogen activator inhibitor, D-dimer, global fibrinolysis, thrombin generation fVII, von-Willebrand Factor and anti-thrombin III and stored serum. *Complications*: cardiopulmonary or neurologic complication within the 3 months after the study period. ROTEM, rotational thromboelastometry

Blood loss is difficult to measure; therefore, we will have a dedicated person available to monitor and register blood loss and measure the size of the excision. To determine the size of the excision, the excision site will be measured using a ruler. To register blood loss, we will use two methods. Firstly, intraoperative blood loss will be estimated by measuring the volume of blood collected in suction canisters, the weight of blood-soaked material (gauzes, pads, etc.), and the volume of adrenalized saline and subtracting the dry weight of these materials and the volume of adrenalized saline used for cleaning the surgical site. Secondly, we will calculate blood loss based on the preoperative hematocrit, postoperative hematocrit, and the intraoperative transfusions using the formula proposed by Camarase et al. in 2006 [21]. We will use this method because intraoperative transfusions are incorporated in the formula [21].

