### Participant timeline {13}

When a potential participant is scheduled for burn excisional surgery, the patient is informed about the study and informed consent is taken. See Fig. 1 for the complete timeline for the participant. Informed consent is usually taken in the 2-3 days before surgery. After consent, the patients are randomized. A blood sample is taken before surgery to establish a baseline. During surgery, two more blood sample will be taken, and one blood sample will be taken 6–12 h after surgery. Hereafter, the study procedure is finished for the patient. After 3 months, the patient will be contacted to inform whether cardiopulmonary of neurologic complications have occurred.

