### Plans to promote participant retention and complete follow-up {18b}

This is not applicable. The whole study period will be performed while the participants are in the hospital, and participants can therefore be directly monitored.

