### Methods in analysis to handle protocol non-adherence and any statistical methods to handle missing data {20c}

The data will be analyzed using an intention-to-treat method without methods to handle missing data.

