### Adverse event reporting and harms {22}

Adverse event (AE), serious adverse events (SAE), and suspected unexpected serious adverse reactions (SUSAR) are monitored and recorded after a patient provides informed consent. Adverse events reported spontaneously by the subject or observed during a routine consultation examination by the investigator, or his staff will be recorded. Adverse events regularly associated with surgery or burn treatment will not be monitored: nausea/vomiting, pain, skin rash of surgery site, diarrhea, edema, hypo-/hypertension, psychosis, delirium. In conformation with the Medical Research Involving Human Subjects ACT, SAE will be reported to the Medical Research Ethics Committee (MREC) within 7 days after first knowledge for SAEs leading to death or that are life threatening and for other SAEs within 15 days of first knowledge. SUSARs will be reported twice yearly as a line list to the MREC. Three months after the intervention, the electronic health record and the participant will be consulted to evaluate possible cardiopulmonary of neurologic complications.

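### The 3-month complication outcome does not solicit isolated deep vein thrombosis, leaves pulmonary embolism ambiguous, and gives death after discharge no defined outcome

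*Protocol article*

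**What the plan says.** **What is solicited.** Outcomes {12} lists one complication outcome after discharge, with cardiopulmonary complication explained as "i.e., arterial embolism)/ neurologic complication (i.e., stroke) (at 3 months after the study procedure". The Fig. 1 legend gives the same two categories without examples: "cardiopulmonary or neurologic complication within the 3 months after the study period". Participant timeline {13} says: "After 3 months, the patient will be contacted to inform whether cardiopulmonary of neurologic complications have occurred". Adverse event reporting {22} adds a second source: "the electronic health record and the participant will be consulted to evaluate possible cardiopulmonary of neurologic complications". The only mortality outcome in {12} is hospital mortality.

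**What is recorded unsolicited.** Section {22} starts adverse event recording at consent: "Adverse events reported spontaneously by the subject or observed during a routine consultation examination by the investigator, or his staff will be recorded". It exempts some events from monitoring: "nausea/vomiting, pain, skin rash of surgery site, diarrhea, edema, hypo-/hypertension, psychosis, delirium". Thrombosis is not on that list.

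**How risk is described elsewhere.** The exclusion criteria rule out acute venous or arterial thrombosis in the 3 months before inclusion. Background and rationale {6a} bases the safety case on large studies of thromboembolic complications, without restricting these to arterial events.

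**Follow-up and missing data.** Section {18b} calls retention not applicable and gives the reason: "The whole study period will be performed while the participants are in the hospital, and participants can therefore be directly monitored". Section {20c} says: "The data will be analyzed using an intention-to-treat method without methods to handle missing data".

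**The concern.** At entry the protocol treats venous thrombosis over a 3-month window as reason enough to exclude a patient. In the 3 months after an antifibrinolytic drug it does not ask about it. A deep vein thrombosis without embolism is neither a cardiopulmonary nor a neurologic complication, so a study team member who follows the text exactly has no prompt to ask about it or look for it in the record.

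Two neighbouring gaps arise from the same wording. Pulmonary embolism fits the word cardiopulmonary, but not the explanation attached to that word in {12}. A death after discharge but within 3 months belongs to no defined outcome, because mortality is counted in hospital only.

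At stake is whether the trial's harm table gives a full and comparable count of thrombotic events and deaths per arm. There is no monitoring committee {21a} and no interim analysis {21b}, so the 3-month check is the one solicited look at harm after discharge.

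**Working it through.** The finding is one of definition, so the main check sets the sections side by side. The arithmetic only gives scale.

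**1. Coverage by event type**

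| Event within 3 months | Outcome {12} | Fig. 1, {13}, {22} 3-month check | Unsolicited recording {22} |
|---|---|---|---|
| Arterial embolism | named | within cardiopulmonary/neurologic, depending on site | yes |
| Stroke | named | yes (neurologic) | yes |
| Pulmonary embolism | ambiguous: fits cardiopulmonary, not its gloss | yes on the plain word | yes |
| Isolated deep vein thrombosis | no | no | yes, if reported or observed |
| Death in hospital | yes, separate outcome | not named | yes, as a serious event |
| Death after discharge | no | not named | yes, if it becomes known |

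The unsolicited route is weaker for deep vein thrombosis. It relies on spontaneous report or routine observation, and pain and edema, which can be its presenting signs, are on the unmonitored list. A diagnosed thrombosis remains recordable.

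**2. Section {18b} against {12}, {13} and {22}**

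Section {18b} places the whole study period in hospital. Section {13} says the study procedure ends with the sample taken 6–12 h after surgery and then sets a contact at 3 months. {12} has an outcome at that time. A plan for completing follow-up is therefore applicable.

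**3. Scale**

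Inputs from Sample size {14}: mean 194 and SD 81 ml/% BSA, 25% reduction, type I error 5% (two-sided assumed), power 80%, dropout 5%.

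- Difference: 0.25 × 194 = 48.5.
- Per arm, normal approximation: 2 × (1.960 + 0.842)² × (81/48.5)² = 43.8, so 44. The t-test calculation gives 44.8, so 45, as stated.
- With dropout: 90/0.95 = 94.7, so 95, as stated.

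The sample size reproduces and this point does not affect it. The documents give no rate of venous thrombosis, so I assume 1% to 10%. Expected events are 95 × p. Power is for p against 2p with 47 per arm, two-sided 5%, normal approximation.

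| Assumed rate p | Expected events in 95 | Power to detect 2p |
|---|---|---|
| 1% | 0.95 | 5.9% |
| 2% | 1.9 | 8.2% |
| 5% | 4.75 | 14.8% |
| 10% | 9.5 | 27.1% |

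For precision, zero events in 45 patients gives an exact two-sided 95% upper limit of 1 − 0.025^(1/45) = 7.9%. If 5 patients in an arm could not be ascertained (assumption), 1 − 0.025^(1/40) = 8.8%. The 7.9% reflects sample size and would not change with a better definition.

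**The case against.** The strongest defence is that little is actually lost.

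- **Venous events are recordable.** Adverse and serious adverse events are collected from consent and thrombosis is not exempt. This stands. A reader might infer that venous thrombosis will go uncounted, but the text supports only that it is unsolicited and not an outcome.
- **The abbreviation i.e. is used loosely.** In the intervention description the article follows it with a list ending in etc., so the gloss in {12} may be meant as an example. This is a fair reading and keeps pulmonary embolism inside the outcome. It does not bring in isolated deep vein thrombosis, which fits neither category with or without the gloss.
- **Unreached patients are not simply lost.** It is tempting to combine {18b} with {20c} and conclude that they drop out of the comparison. Section {22} plans a health-record check as well as the contact, so the documents do not support that.
- **Section {18b} cancels nothing.** The article tends to use study period for the in-hospital phase, and the 3-month contact still stands in {13} and {22}. This is right: it is a wording conflict, and it bears on all 3-month events rather than venous ones in particular.
- **No direction of bias is shown.** Patients, treating team and outcome assessors are blinded {17a}, and nothing indicates that ascertainment would differ by arm. One cannot say the drug would look safer.
- **Other harm comparisons exist.** Hospital mortality is one, so the 3-month check is not the only systematic one.

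One could add that an article condenses the full protocol. That would excuse missing detail, but here the article states the outcome and repeats the same two categories in three other places.

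**Conclusion.** The point holds in a limited form. As stated, the solicited 3-month outcome omits isolated deep vein thrombosis, is ambiguous on pulmonary embolism and leaves death after discharge without a defined outcome. This sits badly with the protocol's own exclusion criterion and safety rationale. The consequence is less complete capture of these events, not their certain loss.

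Its size cannot be fixed from the documents. On an assumed rate of 1% to 10%, it concerns about 1 to 10 events in the whole trial, too few for a useful test. The primary outcome, its sample size and its analysis are unaffected. It is a worthwhile and inexpensive improvement in harm reporting. It does not threaten the trial's main conclusion.

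**What to change.** 1. In {12}, define the 3-month outcome as any of: an arterial or venous thromboembolic event (including deep vein thrombosis and pulmonary embolism), stroke or other neurologic complication, other cardiopulmonary complication, or death. Replace the i.e. glosses with this definition and use it in the Fig. 1 legend, {13} and {22}.
2. Check for each component in both the participant contact and the health-record review already planned.
3. Report, per arm, the number of patients ascertained at 3 months alongside the number with each event.
4. Reword {18b} so that it agrees with the 3-month follow-up in {12}, {13} and {22}, and say how completion of that follow-up is secured.

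**Cost.** One or two added questions in an existing contact and a protocol wording change. Inclusion began in December 2021, so patients already past 3 months would need a record check for the added events, and their data may be less complete than those of patients asked prospectively.

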### Participant timeline {13}

When a potential participant is scheduled for burn excisional surgery, the patient is informed about the study and informed consent is taken. See Fig. 1 for the complete timeline for the participant. Informed consent is usually taken in the 2-3 days before surgery. After consent, the patients are randomized. A blood sample is taken before surgery to establish a baseline. During surgery, two more blood sample will be taken, and one blood sample will be taken 6–12 h after surgery. Hereafter, the study procedure is finished for the patient. After 3 months, the patient will be contacted to inform whether cardiopulmonary of neurologic complications have occurred.

### Sample size {14}

In a small retrospective group of 109 patients (unpublished) with ≥ 250 ml blood loss from Burn Centre Rotterdam, we found a mean blood loss of 1.01 ± 0.56 ml/cm^2^ or 194 ± 81 ml/% BSA excised. In a small blinded RCT study, Jennes et al. found a reduction of 36% in blood loss in 27 tangential burn wound excisions when administering tranexamic acid [12]. A small RCT with 50 patients performed in India showed a reduction of 41% blood loss in burn patients when using tranexamic acid [13]. Orthopedic literature shows a somewhat more limited blood loss reduction of approximately 25% with the use of 1–2 g of tranexamic acid during surgery [20, 22, 23]. Therefore, based on a mean blood loss of 194 ml/% BSA excised with an SD of 81 ml, demonstrating a 25% reduction in blood loss with type I and type II error rate of 5% and 20% respectively, we require 45 patients per arm, for a total of 90 patients. Taking a dropout rate of 5% into account, we aim to include 95 patients in our study.

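### The two SDs quoted for the same 109 patients imply different relative spreads (55% and 42%), so the SD behind the stated 80% power needs reconciling; power would be about 56% if the per-cm² spread applies

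*Protocol article*

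**What the plan says.** The primary outcome (Outcomes {12}) is "The volume of blood loss in milliliter/% BSA excised measured during surgery". The Sample size {14} section takes its planning values from one unpublished single-centre series, described as "In a small retrospective group of 109 patients (unpublished) with ≥ 250 ml blood loss from Burn Centre Rotterdam", and reports for it: "we found a mean blood loss of 1.01 ± 0.56 ml/cm^2^ or 194 ± 81 ml/% BSA excised". The calculation then proceeds "based on a mean blood loss of 194 ml/% BSA excised with an SD of 81 ml, demonstrating a 25% reduction in blood loss". The significance level is set at 5% and the power at 80%. This leads to 45 per arm, 90 in total, and 95 after allowing for 5% dropout.

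On the area itself, Intervention description {11a} says in the text below the Fig. 1 legend: "To determine the size of the excision, the excision site will be measured using a ruler". The article does not say how the ruler measurement becomes % BSA in the trial, or how area and % BSA were obtained in the retrospective series.

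**The concern.** For a given patient, loss per % BSA is loss per cm² multiplied by one hundredth of that patient's body surface in cm². If both figures describe the same patients and the same excised areas, the two relative spreads can differ only through variation in body surface. Multiplying by a second varying quantity normally widens the relative spread. Here it narrows, from 55% to 42%, and only the narrower figure enters the sample size.

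The stated 80% power rests on that one SD. The article plans no interim analysis and describes no reassessment of the SD, so nothing in it would correct the value during the trial. If the true spread is nearer the per-cm² figure, a null result would be read as stronger evidence against a 25% reduction than the trial can supply.

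**Working it through.** **Inputs.** All come from Sample size {14}: mean 194 and SD 81 ml/% BSA; mean 1.01 and SD 0.56 ml/cm²; 25% reduction; type I error 5%; power 80%; 45 per arm. The section does not state whether the test is two-sided. Two-sided is assumed because it reproduces the printed number; the one-sided normal approximation would give 35 per arm.

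**1. The plan's own figure.** Difference = 0.25 × 194 = 48.5 ml/% BSA. Standardised difference = 48.5/81 = 0.599. A two-sample t-test needs 44.8 per arm, rounded up to 45, and power at 45 per arm is 80.2%. Dropout: 90/0.95 = 94.7, so 95. The printed numbers reproduce.

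**2. Do the two descriptions agree?**
- Means: 194/1.01 = 192 cm² per % BSA, a body surface of about 1.92 m². They agree.
- Coefficients of variation: 81/194 = 41.8% and 0.56/1.01 = 55.4%. They do not. An ml/cm² SD in proportion to 81 would be 0.418 × 1.01 = 0.42, not 0.56.

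**3. Can body-surface conversion explain the gap?** Assume lognormal data, with log-SD = √ln(1 + CV²). This gives 0.518 per cm² and 0.401 per % BSA. With t the log-SD of body surface and ρ its log-scale correlation with loss per cm²:

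0.401² = 0.518² + t² + 2ρ(0.518)t

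The smallest t that allows a solution is 0.518 − 0.401 = 0.117, at ρ = −1. The documents give no value for t, so a range is shown:

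| t | required ρ |
|---|---|
| 0.10 | −1.13 (no solution) |
| 0.12 | −0.98 |
| 0.15 | −0.84 |

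If body surface is instead unrelated to loss per cm² and has a CV of 8% to 15%, the ml/% BSA spread rises to a CV of 56% to 58% (SD 109 to 113 ml). With an assumed ρ of −0.5 over the same range, the CV is 49% to 51% (SD about 95 to 99 ml).

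**4. Power if the per-cm² relative spread applies.** The equivalent SD is 0.554 × 194 ≈ 108 ml/% BSA. Standardised difference = 0.2525/0.56 = 0.451. With 45 per arm:
- power for a 25% reduction: 56.2%;
- patients for 80% power: 78.2, so 79 per arm;
- standardised difference detectable with 80% power: 0.597, which is 0.597 × 0.56/1.01 = 33.1% of the mean.

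**5. Other bases, 45 per arm, 25% reduction.**

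| Basis | CV 42% | CV 55% |
|---|---|---|
| Equal SDs (as planned) | 80% | 56% |
| Treated-arm SD falls by 25% with the mean | 89% | 67% |
| t-test on the log scale | 92% | 74% |

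Between the two quoted spreads, with equal SDs, power is 72% at an SD of 90 and 62% at 100.

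**The case against.** The strongest reply is that the plan uses the SD on the primary outcome's own scale, which is correct practice, and that its arithmetic is right. No section makes ml/cm² an outcome. This stands: the use of 81 rather than 0.56 is not an error in itself.

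A reader might go further and infer that the trial has 56% power and not 80%. The documents do not support that. If the wrong figure is 0.56, which the calculation never uses, 81 holds and so does 80%. The same is true if the trial will obtain % BSA in the way the retrospective file did. The ruler does not settle the matter, because the article does not say how either set of areas was converted. A condensed article may leave that detail to the full protocol or to the standard operating procedure it mentions.

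Nor is it right to call the two SDs impossible together. The bound in step 3 assumes lognormal data, whereas the section reports arithmetic means and SDs. A constructed set of 109 patients, in which three heavy bleeders have small body surfaces, comes close to both printed results with a body-surface CV of only 5%. That needs an unusual handful of patients, and nothing in the article suggests it occurred, but it rules out the word impossible.

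Finally, even with the wider spread, 45 per arm gives about 86% power for a 36% reduction and 93% for 41%, the effects the section cites from two burn trials. That limits the consequence. The plan nevertheless powers on 25%, and its claim concerns 25%.

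**Conclusion.** The point holds as an unresolved conflict in the planning data. One sentence gives two relative spreads for the same patients, and ordinary body-surface conversion does not reconcile them. Probably one SD is wrong or the two areas were obtained differently; the article does not show which.

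The consequence is conditional. Power for a 25% reduction with 45 per arm is 80% if SD 81 is confirmed. It is about 56% if the trial's ml/% BSA carries the per-cm² spread, or about 67% if the treated-arm SD shrinks with the mean, and the reduction detectable at 80% power then moves from 25% to about 33%. These figures assume a two-sided 5% t-test with 90 evaluable patients; the 56% and 33% also assume equal SDs in the two arms. The judgement that the spreads are hard to reconcile rests on roughly lognormal loss and on assumed body-surface variation of the order shown.

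**What to change.** In the 109-patient file, recompute both SDs, with % BSA derived as the trial will derive it, and state that derivation in one sentence. Correct whichever printed figure is wrong. If both are right, say why they differ. Then restate Sample size {14} with the reconciled SD: either confirm 80% power for a 25% reduction or, if the per-cm² spread stands, state about 56% power for 25% and 80% power for about 33% with 90 evaluable patients.

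The cost is two summary statistics from data already held and a wording change, which can be settled before unblinding. No extra patients and no change to the endpoint are needed. The one downside is that the stated power may become less favourable.
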